### Comparison

The 10 primary healthcare centres in the intervention arm will be compared with the 10 primary healthcare centres in the control arm. The control arm will receive no intervention and proceed with usual care.

### Quantitative indicators

Indicators were developed to balance input and process indicators, such as measurement of risk factors and calculation of risk scores, with output (eg, prescribing) and outcome (eg, blood pressure control) indicators. While one of the objectives of this evaluation is to determine the ability to measure these indicators based on routine paper records, we used our existing knowledge of the health system to design indicators which were valuable and likely to be feasible to calculate. Table 1 shows the indicator, the question the indicator seeks to answer and the respective numerator and denominator definitions that will be used in the calculations.

**Table 1 T1:** Indicators, their numerators and denominators and questions the indicators answer

Question	Indicator	Numerator	Denominator
Are risk factors being measured?	Proportion of eligible patients who have all risk factor values recorded as required for calculation of risk score.	Patients aged 40 years or older who have visited in the last 12 months who have all measurements required for calculation of risk score within 12 months of the most recent date of visit.	Patients aged 40 years or older who have visited in the last 12 months.
Are risk factor measurements being converted to a total risk score?	Proportion of patients aged 40 years or older who have visited in the last 12 months who have all measurements required for calculation of risk score within 12 months of the most recent date of visit, which have a documented risk score.	Patients aged 40 years or older who have visited in the last 12 months who have all measurements required for calculation of risk score within 12 months of the most recent date of visit, which have a documented risk score.	Patients aged 40 years or older who have visited in the last 12 months who have all measurements required for calculation of risk score within 12 months of the most recent date of visit.
Are risk scores calculated correctly?	Proportion of patients aged 40 years or older who have visited in the last 12 months who have all measurements required for calculation of risk score within 12 months of the most recent date of visit, which have a documented risk score that is correct.	Patients aged 40 or older who have visited in the last 12 months who have all measurements required for calculation of risk score within 12 months of the most recent date of visit, which have a documented risk score that is correct.	Patients aged 40 or older who have visited in the last 12 months who have all measurements required for calculation of risk score within 12 months of the most recent date of visit, which have a documented risk score.
Are patients being risk scored?	Proportion of eligible patients with a documented risk score.	Patients aged 40 years or older who have visited in the last 12 months with a documented risk score.	Patients aged 40 years or older who have visited in the last 12 months.
Are risk scores calculated correctly?	Proportion of eligible patients with a documented risk score that is correct.	Patients aged 40 years or older who have visited in the last 12 months with a documented risk score that is correct.	Patients aged 40 years or older who have visited in the last 12 months with a documented risk score.
Are statins prescribed to the correct patients?	Proportion of eligible patients prescribed a statin.	Patients with existing CVD, patients with diabetes aged 40 years or older with high LDL values (as defined based on total CVD risk of SCORE 10%–14% in LDL≥2.6 mmol/L; with very high risk SCORE≥15% in LDL≥1.8 mmol/L), or patients with a SCORE of ≤9% and LDL≥2.6 or total cholesterol≥7.2, or patients with a SCORE of 10%–14% and LDL≥1.8 or total cholesterol≥7.2 mmol/L, or patients with a SCORE of ≥15%, prescribed a statin.	Patients with existing CVD, patients with diabetes aged 40 years or older with high LDL values (as defined based on total CVD risk of SCORE 10%–14% in LDL≥2.6 mmol/L; with very high risk SCORE≥15% in LDL≥1.8 mmol/L), or patients with a SCORE of ≤9% and LDL≥2.6 or total cholesterol≥7.2, or patients with a SCORE of 10%–14% and a LDL≥1.8 or total cholesterol≥7.2 mmol/L, or patients with a SCORE of ≥15%.
Are statins prescribed correctly based on documented risk score?	Proportion of patients eligible based on documented risk score prescribed a statin.	Patients with a documented risk score as very high risk SCORE≥15% prescribed a statin.	Patients with a documented risk score as very high risk SCORE≥15%.
Are patients with existing disease, who do not require the calculation of a risk score to prescribe satins, prescribed statins?	Proportion of patients with existing CVD prescribed a statin.	Patients with existing CVD prescribed a statin.	Patients with existing CVD.
Is the blood pressure of high-risk patients controlled?	Proportion of high-risk patients (SCORE≥15% or DM and age over 40 years) whose last two recorded blood pressure measurements were <130/80 mm Hg.	Patients with a true risk score indicating a very high risk (SCORE≥15%) or DM and age over 40 years whose last two documented blood pressure readings were <130/80 mm Hg.	Patients with a true risk score indicating a very high risk (SCORE≥15%) or DM and age over 40 years.
Is the blood pressure of low-risk patients controlled?	Proportion of low-risk patients (SCORE<15%) whose last two recorded blood pressure measurements were <140/90 mm Hg.	Patients with a true risk score indicating <15% whose last two documented blood pressure readings were <140/90 mm Hg.	Patients with a true risk score indicating <15%.
Are patients with existing CVD prescribed basic medications to reduce risk?	Proportion of patients with existing CVD prescribed a statin and aspirin and blood pressure-lowering treatment.	Patients with existing CVD prescribed a statin and aspirin and blood pressure-lowering treatment.	Patients with existing CVD.
Is the blood glucose of patients with diabetes controlled?	Proportion of patients with diabetes with glycaemic control as defined by last two HbA1c measurements.	Patients with type 2 diabetes whose last two HbA1c measurements were below personal target as defined by MDA-adapted WHO PEN protocol 1.	Patients with type 2 diabetes.
Is the blood pressure of patients with hypertension controlled?	Proportion of patients with confirmed hypertension whose systolic blood pressure is <140/90 mm Hg at last two visits.	Patients with confirmed hypertension whose last two blood pressure readings were <140/90 mm Hg.	Patients with confirmed hypertension.
What is the prevalence of high blood pressure?	Proportion of people whose last two systolic blood pressure reading are 140 mm Hg or above.	Patients whose last two systolic blood pressure readings were ≥140 mm Hg.	All patients aged over 18 years.

CVD, cardiovascular disease; DM, diabetes mellitus; HbA1c, glycated haemoglobin; LDL, low-density lipoprotein; SCORE, Systematic COronary Risk Evaluation.

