### Essential interventions to prevent cardiovascular diseases in primary healthcare

In order to build capacity in primary healthcare and ultimately prevent premature mortality from CVD in MDA, a study was envisioned to adapt and pilot the WHO Package of Essential NCD Intervention from Primary Healthcare in Low Resource Settings (WHO PEN).^3^ WHO PEN includes simplified clinical protocols which together cover the integrated management of hypertension and diabetes, as well as education and counselling on healthy behaviours aimed to prevent CVD. The central strategy of this integrated approach is the use of total cardiovascular risk assessment to stratify and target individuals at high CVD risk, a process considered to be a ‘best buy’ intervention by WHO.^5^

These interventions are aimed at tackling areas identified in a 2014 WHO assessment of challenges and opportunities for better NCD outcomes in MDA.^13^ This includes shortcomings among health workers in the identification and management of individuals with increased cardiovascular risk. The interventions are expected to add to the current quality of care by targeting interventions (non-pharmacological and/or pharmacological) to those at highest risk who stand to gain the most in absolute cardiovascular risk reduction, while also emphasising improvements in the organisation of care. The intervention also includes practical face-to-face training and follow-up implementation support. Current practice underuses these medical strategies and guidelines (eg, CVD risk score directed primary prevention), in addition to limited task sharing with non-physician health workers (eg, nurses) in these care pathways.^13^ At the study’s inception, there were no known developments beyond the scope of this project that could change clinical practice for NCDs in primary healthcare.

Since the use of WHO PEN was unprecedented in MDA, the Ministry of Health, Labour and Social Protection convened a national steering group to lead the adaptation and pilot process, with the goal of using the findings for future health systems development. Led by the primary healthcare division of the Ministry of Health, the steering group comprises representatives from the Nicolae Testemitanu State University of Medicine and Pharmacy and the National Public Health Agency. The national steering group is supported by an international team of experts coordinated jointly by the WHO Regional Office for Europe and WHO Country Office in MDA.

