### Data collection and management

#### Quantitative data collection tool

A standardised data collection template has been developed for extracting anonymised patient data from individual paper records (table 2). An online version was also made to allow for data entry on a computer or smartphone. It is estimated to take 15 min to extract data from one patient record since the records are made of blank paper with no formal structure or organisation of health data.

**Table 2 T2:** Standardised data collection form used to extract data from individual patient records

Data collection question	Answer
What is your name? (Name of person extracting data)	
Date of data extraction (MM-DD-YYYY)	
Write the clinic name	
Is this a duplicate extraction?	
If it is a duplicate extraction, enter the number you and your extraction partner have assigned to this file.	
Date of birth (MM-DD-YYYY)	
Sex (M/F)	
Smoking status (Y/M)	
Diagnosis of hypertension (Y/N)	
Date of hypertension diagnosis (MM-DD-YYYY)	
Can you find one or more blood pressure readings? (Y/N)	
Most recent systolic blood pressure	
Most recent diastolic blood pressure	
Date of the most recent blood pressure measurement (MM-DD-YYYY)	
Can you find a second most recent blood pressure reading? (Y/N)	
Second most recent systolic blood pressure	
Second most recent diastolic blood pressure	
Date of the second most recent systolic blood pressure (MM-DD-YYYY)	
Diagnosis of diabetes (type 1, type 2, no)	
Can you find one or more glycated haemoglobin (HbA1c) measurements? (Y/N)	
Most recent HbA1c reading (mmol/mol)	
Date of the most recent HbA1c measurement? (MM-DD-YYYY)	
Can you find another HbA1c measurement? (Y/N)	
Second most recent HbA1c reading (mmol/mol, otherwise specify unit)	
Date of the second most recent HbA1c reading? (MM-DD-YYYY)	
Can you find one or more total cholesterol measurements? (Y/N)	
Most recent total cholesterol reading (mmol/L)	
Date of the most recent cholesterol reading (MM-DD-YYYY)	
Can you find another cholesterol measurement? (Y/N)	
Second most recent cholesterol reading (mmol/L)	
Date of the second most recent cholesterol reading (MM-DD-YYYY)	
Was the patient prescribed a statin? (Y/N)	
What was the date of the statin prescription? (MM-DD-YYYY)	
What was the drug and dose?	
Does the patient have existing cardiovascular disease (CVD)? (Y/N)	
State the type of CVD	
Has the patient been prescribed acetylsalicylic acid (ASA or aspirin)? (Y/N)	

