#### Method of randomly sampling patient records

A random sample of the records of patients aged over 18 years, who have visited the medical facility within the past 12 months, will be taken. Since medical records in MDA are organised alphabetically on shelves, we created a randomly generated list of alphanumeric combinations that allowed for the selection of patient charts at random. For example, an alphanumeric code of ‘C24’ would correspond to the 24th patient chart in the section of last names starting with the letter C.

The list will be followed in the order that it was generated so as to prevent selection bias. The randomly selected chart will then be checked to see if it meets two inclusion criteria^1^: the patient is aged 18 years or older and^2^ the patient visited the health centre within the last 12 months. If the record meets these criteria, data will then be extracted. If it does not, it will be returned to the shelf and the next alphanumeric code on the randomly generated list will be used. This process will be repeated in each clinic until a sample size of 1.2% of the patient population in each clinic is sampled. This proportion was chosen pragmatically such that the average sample per primary healthcare centre would equal 100 unique patients.

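### Two risk-scoring indicators in Table 1 count patients with existing CVD in their denominators, so their level and the absolute arm difference depend on CVD case mix if those patients are scored less often

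*Protocol article*

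**What the plan says.** The Quantitative indicators section states that the numerators and denominators in Table 1 are the ones to be used in the calculations, so they are working definitions.

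- **Being risk scored.** The indicator is "Proportion of eligible patients with a documented risk score". Its denominator is all "patients aged 40 years or older who have visited in the last 12 months". The word eligible is given no further content.
- **Conversion of measurements to a score.** The denominator is the part of that group with every measurement the score needs. The numerator is those who also have a documented score.
- **Statin row for existing CVD.** It asks "Are patients with existing disease, who do not require the calculation of a risk score to prescribe satins, prescribed statins". The general statin row also lists existing CVD as a route to eligibility separate from the SCORE bands.
- **Purpose of the score.** The background section on essential interventions gives "CVD risk score directed primary prevention" as an example of what current practice underuses.
- **Sampling and form.** Records are sampled on adult age and on whether "the patient visited the health centre within the last 12 months", so CVD patients are not removed at that stage. The extraction form asks "Does the patient have existing cardiovascular disease (CVD)? (Y/N", so the group can be identified.

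The Data analysis section uses the health-centre proportion with a documented score as its example of an outcome. It plans to compare changes in the indicators between arms and to fit logistic models adjusted for age and gender.

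**The concern.** The table is not consistent about whom the score is for. The statin rows and the background text set patients with existing CVD apart from score-directed decisions. The two scoring rows nevertheless count each such patient without a score in the same way as an unscored patient in primary prevention.

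If clinics score CVD patients less often for that reason, three things follow:

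- A clinic that scores every other patient still falls short of 100%, which could be read as incomplete implementation when national scale-up is considered.
- The indicator varies with the clinic's CVD share as well as with what the staff do. Randomisation is stratified only on patients per family doctor, and the models adjust only for age and gender, so CVD share is not directly controlled.
- The absolute difference between arms shrinks.

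**Working it through.** The plan states no expected indicator value, effect size or power, so there is no figure of its own to reproduce. The check is algebraic, with assumed inputs.

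**Inputs**
- c: share with existing CVD in the row's denominator. Not given; assumed 5% to 30%. For orientation, the introduction reports 23.0% of people aged 40–69 with a 10-year risk above 30%, a figure that includes existing CVD. It is therefore an upper bound for CVD in that population. Clinic attenders and patients aged 70 or older could exceed it.
- f: scoring rate in CVD patients relative to CVD-free patients. Not given; taken as 0, 0.5 and 1.
- p1, p0: scoring rates in CVD-free patients in the intervention and control arms. Assumed 50% and 10% for illustration, a 40-point difference.
- c and f are taken as equal in both arms unless stated.

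**Formula.** The indicator in an arm is p × [(1 - c) + c × f]. Hence:
- value when all CVD-free patients are scored (p = 1): (1 - c) + c × f
- absolute difference: (p1 - p0) × [(1 - c) + c × f]
- risk ratio: p1/p0, because the bracket cancels

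**Results**

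| c | Highest value, f = 0 | Difference, f = 0 | Difference, f = 0.5 | Difference, f = 1 |
|---|---|---|---|---|
| 5% | 95% | 38 points | 39 points | 40 points |
| 10% | 90% | 36 points | 38 points | 40 points |
| 20% | 80% | 32 points | 36 points | 40 points |
| 30% | 70% | 28 points | 34 points | 40 points |

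Example: c = 30%, f = 0 gives 40 × 0.70 = 28; c = 30%, f = 0.5 gives 40 × (0.70 + 0.15) = 34. At c = 23% and f = 0 the difference is 40 × 0.77 = 30.8 points.

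**Relative measures.** The risk ratio is 5.0 throughout. The unadjusted odds ratio is (0.50/0.50)/(0.10/0.90) = 9.0 without CVD patients. With f = 0 it is about 8.6, 8.3, 7.7 and 7.2 for c = 5%, 10%, 20% and 30%. For the last, (0.35/0.65)/(0.07/0.93) = 7.2.

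**Unequal CVD share.** With f = 0 and shares of 15% (intervention) and 25% (control), the difference is 0.85 × 50 - 0.75 × 10 = 35 points. With the shares reversed it is 0.75 × 50 - 0.85 × 10 = 29 points.

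**Other rows in the group.** The two rows on correct calculation have only patients with a documented score in the denominator, so an unscored CVD patient does not enter them. The row "Proportion of eligible patients who have all risk factor values recorded as required for calculation of risk score" concerns measurement. Nothing in the document suggests that risk factors may go unmeasured in CVD patients.

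**The case against.** A reader might infer that the plan marks correct care as failure. The document does not go that far. The row on existing disease says only that no score is needed for the statin decision, and the primary-prevention remark is an example that excludes nobody. Who should be scored is set by the nationally adapted protocols, which are not shown. That objection stands: the reading is a reasonable inference, not a stated rule.

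A reader might also take the fault to run through all five risk-factor and risk-score rows. It does not, as the check of the other three rows shows.

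Nor is dilution certain. It disappears if CVD patients are scored as often as others. With equal c and f it leaves the risk ratio alone, moves the odds ratio only modestly, and attenuates a real contrast without creating a false one.

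The stakes are also limited. No indicator is designated primary, the arm comparison is a secondary objective, and this is a feasibility pilot whose size was set pragmatically.

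Finally, a denominator of age and a recent visit is simpler to apply. CVD status has to be found in unstructured paper records, and training could change how fully it is recorded. This is a real drawback of restriction, and a reason to keep the unrestricted figure alongside.

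None of this settles who counts as eligible in the two remaining rows.

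**Conclusion.** The point holds for two rows: conversion of measurements to a score, and the proportion of patients scored. Their denominators include patients with existing CVD, while other parts of the same document treat those patients as outside score-directed decisions on statins. If they are scored less often, the highest attainable value falls below 100%, the indicators respond to CVD case mix, and the absolute arm difference is reduced.

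The size cannot be fixed from the document. It depends on an assumed CVD share of 5% to 30%, an assumed relative scoring rate, and equality of both across arms. Over that range a 40-point difference loses between 2 and 12 points if no CVD patient is scored, between 1 and 6 points at half the rate, and nothing at equal rates.

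The evidence supports an unresolved definition of eligibility with a conditional loss on the absolute scale. It does not support a claim that the arm comparison is invalid or that care is necessarily misclassified.

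**What to change.** Calculate the two rows in patients aged 40 or older without existing CVD, applying the restriction to numerator and denominator and using the CVD item already on the extraction form. Report the version with all patients aged 40 or older beside it. Presenting both rows by CVD status would serve equally well. State what eligible means in these rows, and reconcile it with the statin row for existing CVD and with the adapted protocol. The measurement row and the two accuracy rows need no restriction, though they may also be shown by CVD status.

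The change needs new wording in two table rows and no new data. It leaves fewer records per clinic in those rows, by the CVD share. It also makes the result depend on how well CVD is recorded in paper charts, which could differ by arm after training. The unrestricted figure lets a reader see whether that matters.

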#### Step 6: collection of follow-up data

After 12 months, using the same method and data collection instruments used to collect baseline quantitative data (step 3), data will again be extracted from randomly selected individual paper-based patient records from all 20 healthcare centres. Five primary healthcare centres from the intervention arm will be selected by the national steering group for one-on-one semi-structured interviews with health staff. This will be supplemented by inviting a selection of staff from all 10 health centres in the intervention arm to participate in focus groups. Together, these qualitative data will be analysed thematically for explanatory themes.

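### Four of the 14 Table 1 indicators cannot be calculated as defined, because the Table 2 extraction form has no LDL field and no date of last visit

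*Protocol article*

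**What the plan says.** Under Quantitative indicators, the protocol article presents Table 1 as the "numerator and denominator definitions that will be used in the calculations". Rows are numbered here from the top of that table, 1 to 14.

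- **Row 6 (statins to the correct patients).** The eligible group starts with "Patients with existing CVD, patients with diabetes aged 40 years or older with high LDL values". It then adds SCORE ≤9% with LDL ≥2.6 or total cholesterol ≥7.2, SCORE 10–14% with LDL ≥1.8 or total cholesterol ≥7.2, and SCORE ≥15%.
- **Rows 1 to 3 (all risk factors measured; converted to a score; score correct).** Each counts measurements taken "within 12 months of the most recent date of visit".
- **Row 12 (glycaemic control).** The last two HbA1c values must be "below personal target as defined by MDA-adapted WHO PEN protocol 1".

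Under Quantitative data collection tool, the article says: "A standardised data collection template has been developed for extracting anonymised patient data from individual paper records". Table 2 prints that form. Its lipid block opens with "Can you find one or more total cholesterol measurements? (Y/N" and goes on to the most recent and second most recent total cholesterol. LDL does not appear. Dates are recorded for the extraction, the hypertension diagnosis, each measurement, each prescription and the documented score, but not for the last visit. Smoking is one field with the printed codes Y and M. Step 6 repeats the exercise after 12 months "using the same method and data collection instruments used to collect baseline quantitative data".

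**The concern.** An indicator can be computed only from what the extractors write down. If a definition rests on an item that the form never asks for, no analysis plan can recover it; someone has to go back to the charts. The work involved is about 20 clinics × 100 records × 2 time points = 4,000 extractions, taking the article's intended average of 100 patients per centre. Because the instrument is reused, an item missing at baseline is also missing at follow-up.

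Two things are at stake. The statin-eligibility proportion would be computed on a different population from the one defined. And one primary objective is to learn whether the data for future effectiveness studies can be obtained from the paper records: a form that does not ask for LDL or the visit date cannot answer that for those two items.

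**Working it through.** The plan states no figure to reproduce. The check sets each element of the 14 Table 1 definitions against the Table 2 fields.

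| Element needed | Table 1 rows | On the form | Result |
|---|---|---|---|
| LDL value | 6 | Total cholesterol only | Not computable as defined |
| Date of most recent visit | 1, 2, 3 | Extraction and item dates only | Not computable as defined |
| Smoking: yes, no or not recorded | Rows using all measurements or a correct or true score, if smoking is a SCORE input | Two codes, no found/not-found question, no date | Probable gap |
| Personal HbA1c target | 12 | Two HbA1c values, no target | Depends on the adapted protocol, not shown |

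Certain failures: 1 + 3 = 4 of 14.

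**LDL, row 6.** Without LDL, the eligible group can be built only from existing CVD, SCORE ≥15%, or total cholesterol ≥7.2. A patient without CVD, with SCORE ≤9%, LDL ≥2.6 and total cholesterol below 7.2, is eligible by definition and invisible on the form. The same holds for SCORE 10–14% with LDL ≥1.8 and total cholesterol below 7.2. These patients drop out of both numerator and denominator.

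Let w be the share of truly eligible patients lost in this way, p₁ the statin proportion among those kept and p₂ among those lost. Then

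- proportion as defined = (1 − w)p₁ + w·p₂
- proportion observed = p₁
- error = p₁ − [(1 − w)p₁ + w·p₂] = w(p₁ − p₂)

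The documents give neither w nor p₂, so the size and sign of the error are unknown.

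**Visit date, rows 1 to 3.** Let V be the months from last visit to extraction. The sampling screen requires a visit in the last 12 months, so 0 ≤ V ≤ 12. A measurement of age A at extraction qualifies as defined if A ≤ V + 12, so A can reach 12 + 12 = 24 months.

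- With the extraction date as reference, the rule becomes A ≤ 12, and measurements with 12 < A ≤ V + 12 are wrongly excluded.
- Example: last visit 11 months before extraction, cholesterol taken 10 months before that visit. A = 11 + 10 = 21. As defined, 21 ≤ 23 qualifies; by extraction date, 21 > 12 fails.
- Measurements with A ≤ 12 or A > 24 are classified correctly, so the ambiguity is confined to 12–24 months. The other dates on the form narrow it further: if dated entries are made at visits, the last visit is no earlier than the latest of them.

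Row 1 keeps its denominator (age from date of birth, visit from the screen) and would be understated by this substitute. Rows 2 and 3 are conditional on the set that row 1 counts, so their denominators shift too and the direction is not fixed.

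**Second cholesterol reading.** Table 2 spends three fields on it (found, value, date). No Table 1 indicator uses it.

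**Overlap inside row 6.** The diabetes clause covers SCORE 10–14% with LDL ≥2.6 and SCORE ≥15% with LDL ≥1.8. The first lies inside the general 10–14% clause with LDL ≥1.8; the second lies inside the general SCORE ≥15% clause. Read this way, the diabetes clause adds nobody.

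**The case against.** The best defence is that this is a pilot in which the form is itself on trial, that the sample size is pragmatic and that change in performance is only a secondary objective. Statin prescribing is also still measured in rows 7 and 8 and within row 11, none of which needs LDL. For rows 1 to 3 the visit screen protects the row 1 denominator and the error is bounded. All of this stands as a limit on the damage. It does not remove the mismatch: a pilot form cannot test for items it omits, and the optional notes field does not prompt for them. Nor is it a matter of condensation, since both tables are printed and one is offered as the form.

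A reader might infer more than the documents support:

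- **That the primary objective would be answered no because of the form.** Four affected indicators out of 14 do not show that. Rows on existing CVD, on the presence of a documented score, on documented SCORE ≥15% and on blood pressure in hypertension can all be computed.
- **That the HbA1c row also fails.** The adapted protocol is not shown. The form holds date of birth, diabetes type and existing CVD, and the target may follow from such items.
- **That undocumented smoking would be entered as non-smoker and the true score biased low.** The printed code M is unexplained: it may be a misprint for N or may mean missing. A blank is also possible, and the extractors are trained. No direction of bias can be claimed.
- **That the diabetes clause distorts the statin indicator.** A clause that adds nobody changes no count.

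**Conclusion.** The mismatch is real and should be settled before baseline extraction. Four of the 14 indicators (rows 1, 2, 3 and 6) cannot be calculated as defined from the printed form, at either time point. For row 6 the eligible population changes, by an amount that the documents do not allow anyone to compute. For rows 1 to 3 the effect is a bounded misclassification of measurements 12 to 24 months old at extraction, not loss of the indicators.

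This rests on Table 2 being the complete form, as the article presents it. Smoking coding (assuming smoking enters SCORE) and the HbA1c target are probable gaps that need confirmation and are not counted in the four.

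**What to change.** **Before baseline extraction**, add to Table 2:

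1. Most recent LDL with its date. This can take the place of the second total cholesterol reading.
2. Date of the most recent visit. Extractors already check for a visit in the last 12 months, so they have only to write the date down.

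**If extraction has begun**, restate the four definitions to match the fields collected and apply the same wording at both time points. Label row 6 so that it does not claim full LDL-based eligibility. Anchor rows 1 to 3 explicitly on the extraction date. Fields added only at follow-up could inform feasibility but would give no change from baseline.

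**Also:**

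- Give smoking separate codes for yes, no and not recorded, and treat not recorded as missing.
- Confirm that the personal HbA1c target can be derived from fields on the form; if not, add the target or the items that fix it.
- Reconcile the overlapping diabetes and SCORE clauses in row 6 with the adapted protocol. Which threshold is right is not judged here.

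The cost is a few fields and a little extra time on a form estimated at 15 minutes per chart, with the same charts and extractors. Restating the definitions costs only an edit to Table 1.
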